## Abstract

**Introduction:**

Ambulances services are asked to further reduce avoidable conveyances to emergency departments (EDs). Risk of Adverse Outcomes after a Suspected Seizure seeks to support this by: (1) clarifying the risks of conveyance and non-conveyance, and (2) developing a risk prediction tool for clinicians to use ‘on scene’ to estimate the benefits an individual would receive if conveyed to ED and risks if not.

**Methods and analysis:**

Mixed-methods, multi-work package (WP) project. For WP1 and WP2 we shall use an existing linked data set that tracks urgent and emergency care (UEC) use of persons served by one English regional ambulance service. Risk tools are specific to clinical scenarios. We shall use suspected seizures in adults as an exemplar.

*WP1*: Form a cohort of patients cared for a seizure by the service during 2019/2020. It, and nested Knowledge Exchange workshops with clinicians and service users, will allow us to: determine the proportions following conveyance and non-conveyance that die and/or recontact UEC system within 3 (/30) days; quantify the proportion of conveyed incidents resulting in ‘avoidable ED attendances’ (AA); optimise risk tool development; and develop statistical models that, using information available ‘on scene’, predict the risk of death/recontact with the UEC system within 3 (/30) days and the likelihood of an attendance at ED resulting in an AA.

*WP2*: Form a cohort of patients cared for a seizure during 2021/2022 to ‘temporally’ validate the WP1 predictive models.

*WP3*: Complete the ‘next steps’ workshops with stakeholders. Using nominal group techniques, finalise plans to develop the risk tool for clinical use and its evaluation.

**Ethics and dissemination:**

WP1a and WP2 will be conducted under database ethical approval (IRAS 307353) and Confidentiality Advisory Group (22/CAG/0019) approval. WP1b and WP3 have approval from the University of Liverpool Central Research Ethics Committee (11450). We shall engage in proactive dissemination and knowledge mobilisation to share findings with stakeholders and maximise evidence usage.

STRENGTHS AND LIMITATIONS OF THIS STUDYRisk of Adverse Outcomes after a Suspected Seizure will use a ‘cutting-edge’ linked data set that captures service use in one ambulance region using data high in quality and coverage.The parameters of the outcome measures used to describe risks and the variables tested for their ability to predict these outcomes will be informed by stakeholders and service users.The large, pseudoanonymised nature of the linked data set will require the use of a generic definition of an ‘avoidable attendance’ whose validity for suspected seizures is not yet known.As there are no equivalent linked data sets available for other ambulance regions, the validity of the derived prediction models will need to be determined within a cohort of patients treated within the same region, but at a later date.

## Introduction

### Context and drive for health service innovations

Ensuring people ‘get the right care at the right time in the optimal care setting’^1^ is a key ambition of the UK’s National Health Service (NHS). Ambulance services have a role to play. They should only be conveying patients to emergency departments (EDs) if it is clinically appropriate or there is no alternative service to provide safe and ongoing care.

Traditionally, UK ambulance services’ primary roles were to provide emergency call handling and transportation to hospital. However, as the nature of the calls it receives has shifted towards non-life-threatening conditions,^2^ services and the clinicians working within them have needed to evolve.^3^

NHS England and Improvement has identified that ambulance clinicians require more support with their changing role.^4^ Certain presentations continue to be ‘over-conveyed’^5^ and reductions in ambulance conveyance rates are stalling.^6^ At the same time, ambulance services are under pressure to provide a timely response to an increasing number of calls,^7^ while facing increased handover delays at EDs.^8^

Strategies are thus needed to support appropriate and safe decision-making on scene that minimises avoidable conveyance. The Risk of Adverse Outcomes after a Suspected Seizure (RADOSS) project seeks to generate ways of providing ambulance clinicians with this support.

### Why is reducing clinically unnecessary conveyance important?

Clinically unnecessary conveyances to EDs result in ‘avoidable attendances’ (AAs).^9^ An AA is where the patient does not require the facilities of a type 1 ED to manage their healthcare problem. AAs can harm the patient^10^ and have implications for others since they restrict ED capacity.^11 12^ Approximately 15% of ED attendances currently meet O’Keeffe *et al*’s^9^ definition of an AA. In 2021/2022, this equated to ~2.3 million visits.^13^

Patients and the public are broadly supportive of non-conveyance. Research has identified that they are frustrated by inappropriate conveyance to ED and say assessment by an ambulance clinician itself has a therapeutic value.^14–21^

Importantly, UK data indicate non-conveyance following assessment by ambulance clinicians is safe. Overall, 83% of people experience no subsequent health event within 3 days of non-conveyance (9% recontact the ambulance service, 12.6% attend ED, 6.3% are admitted and 0.3% die).^22^

### What is known about how ambulance clinicians decide who to convey?

Systematic reviews^23 24^ highlight the complex nature of conveyance decisions. Factors beyond patient need can affect them. Oosterwold *et al*’s^24^ framework (online supplemental file 1) summarises macro, meso and micro factors. Work has started to address some of these.^10 25 26^ However, given reductions in conveyance have stalled, other factors in the model need addressing.

10.1136/bmjopen-2022-069156.supp1Supplementary data

One factor which has yet to be addressed is that ambulance clinicians can find it difficult to confidently identify cases suitable for non-conveyance. Some report uncertainty regarding the accuracy of their assessments for non-conveyance, and express concern for patient safety and their liability if an incorrect decision is made.^10 27–37^

Their uncertainty is unsurprising. Paramedic education has traditionally focused on life-threatening conditions and transportation; decisions are based on limited clinical information and occur under time pressures. These circumstances can create ‘disproportionate risk aversion’, with patients being conveyed to ED as a precaution or in order to save time.^32 37 38^

### What could help clinicians identify cases suitable for non-conveyance?

Ambulance clinicians are critical of current support, saying non-conveyance guidelines and protocols are difficult to apply to the nuances of cases.^31 33 38 39^ When asked what would help, clinicians identify the development of tools to help them differentiate the needs of individuals as a priority and say the relative risks of non-conveyance for different presentations have also not been fully determined.^10 38 40 41^

Given this, promising ways of supporting clinicians include: (1) securing and disseminating clear evidence on the risks of conveyance and non-conveyance by presentation, and (2) providing a risk prediction tool that would allow clinicians to predict the likelihood that conveyance to ED of the individual they are caring for would result in an AA and the likelihood of them experiencing adverse health events if not conveyed. This direction aligns with recommendations by Lord Carter^42^ and others.^4 26^

### What is a risk prediction tool?

Risk prediction tools use ≥2 pieces of patient data to generate a *personalised* estimate of the likelihood that an individual will experience a certain endpoint within a specified time frame. Currently, there are no prediction tools relating to non-conveyance.^26^ However, evidence suggests they could be developed (see Evidence suggesting a tool predicting benefit/risk of non-conveyance could be developed).

Ambulance clinicians already use such tools to predict other outcomes (eg, ref 43–45) and they want more.^40 46^ The National Ambulance guidelines^47^ currently recommend 11 such tools (none relate to seizures). Risk prediction tools do not replace clinical judgement but support it. There is evidence they can improve patient outcomes and satisfaction and avoid unnecessary care.^48–53^

Methodological standards exist^54^ for their development. To facilitate uptake and sustained use, their development needs to be carefully informed by the views of intended users.^55 56^ There is no single pathway by which a tool enters practice, but good practice states confirmation be obtained that it provides valid predictions on a sample different (in time or place) from the one used for model derivation.^57^

### Evidence suggesting a tool predicting benefit/risk of non-conveyance could be developed

The information used by any risk prediction tool should reflect what is available to the clinician at the time conveyancing decisions are made (and is accessible for derivation). Ambulance clinicians do not typically have access to a patient’s full medical record. What is available is the information they record using structured fields on a patient care record (PCR) about the patient’s demographics, medical history, clinical features, physiological observations as well as details relating to the care provided. Also available is structured dispatch information. Online supplemental file 2 indicates the range of data available.

10.1136/bmjopen-2022-069156.supp2Supplementary data

So far, only a selection of this information has been examined for its relationship to the outcomes of interest. While exploratory in nature, studies have identified that recontact with the urgent and emergency care (UEC) system and death following non-conveyance, and AAs following conveyance, are not random but more common in certain subgroups (eg, patient age, sex, time of call, day of week, presence of comorbidities and social deprivation^5 9 22 58–60^).

A testament to the utility of the information available to ambulance clinicians are Patton and Thakore’s 61 study findings. ED clinicians reviewed ambulance PCRs of patients conveyed to ED and identified those whose attendances they suspected would be AA. This was then repeated when ED clinicians had access to the PCR data *and* ED notes. Clinicians were confident in identifying AAs on the basis of the PCR alone.

### Current project

#### Overview and aims

To address the identified needs and information gaps, the 24-month mixed-methods RADOSS project is being completed. It has the following aims: (1) calculate the risks and benefits of conveyance to hospital after a suspected seizure; (2) create a risk prediction tool that predicts the likelihood that an individual will die and/or recontact the UEC system within 3 (and 30) days if not conveyed and the likelihood that their conveyance to ED would result in an AA; and (3) establish a pathway to clinical implementation of the risk prediction tool and maximise usage of RADOSS findings. The project’s related objectives were noted in table 1.

**Table 1 T1:** The RADOSS project’s aims and objectives and the work packages that address them

Aims	Objectives
(1) Calculate the risks and benefits of conveyance to hospital after a suspected seizure.	a. Describe the characteristics of those conveyed and those not conveyed to ED by one representative English ambulance service (WP1a).
	b. Compare the proportions following conveyance and non-conveyance that die and/or recontact the UEC within 3 (and 30) days (WP1a).
	c. Quantify the proportion of incidents conveyed to ED that meet the definition of an AA (WP1a).
(2) Create a risk prediction tool that predicts the likelihood that an individual will die and/or recontact the UEC system within 3 (and 30) days if not conveyed and the likelihood that their conveyance to ED would result in an AA.	d. Optimise the prediction tool development by completing KE workshops with service users and ambulance and ED clinicians to get views on predictors considered for inclusion in the models, the way the outcome measures of death, UEC recontact and AA are defined and risk score presentation (WP1b).
	e. Develop statistical models to predict a person’s risk of death/recontact with the UEC system within 3 (and 30) days and the likelihood of their attendance at ED being classed an AA if conveyed (WP1a).
	f. ‘Temporally’ validate the predictive models using data from the same ambulance service for a later time period (WP2).
(3) Establish a pathway to clinical implementation of the risk prediction tool and maximise usage of RADOSS findings.	g. Complete ‘next steps’ workshops with stakeholders to finalise plans to refine the tool for clinical use and its evaluation (WP3).
	h. Complete a proactive dissemination and knowledge mobilisation strategy (WP3, WP4).

AA, avoidable attendance; ED, emergency department; KE, Knowledge Exchange; RADOSS, Risk of Adverse Outcomes after a Suspected Seizure; UEC, urgent and emergency care; WP, work package.

Risk prediction tools are specific to clinical scenarios. We are therefore focusing on patients experiencing suspected seizures. Seizures are a topic of interest in their own right but also an ideal exemplar since they are frequently encountered by the service^62 63^ and ‘over-conveyed’.^10^
Table 2 expands on the reasons.

**Table 2 T2:** Reasons why suspected seizures are considered an ideal exemplar

Reason		Detail
1	Frequently seen	Responsible for ~211 000 ‘999’ calls per year in England; 7th most common presentation.^62 63^ Almost all (>97%) receive a face-to-face ambulance response.^103^
2	‘Over-conveyed’	Around 70% of suspected seizure cases are conveyed to ED.^63 103–106^ This is despite national guidelines stating most will not require ED.^47^ Suspected seizures are dramatic and frightening and traditional training emphasises status epilepticus—a rare and life-threating condition. However, most ‘999’ suspected seizures are low risk and persons return to their normal self without intervention.^63^ Most of those presenting have established, treated epilepsy and have experienced an uncomplicated seizure for which they require rest and reassurance.^107^ Seizures currently have the third highest conveyance rate of all presentations.^10^
3	Redeemable cause of avoidable attendance	Clinicians identify suspected seizures as a readily redeemable cause of AAs.^32 33 35 46 108^ At a 2016 International League Against Epilepsy run research priority event, clinicians identified developing a risk tool to support conveyance decisions as a priority.^46^
4	*‘*Alternative care pathways’ available	Alternative care pathways are becoming available for clinicians to use.^109 110^ They could, unlike visits to ED,^111^ prompt improvements in ambulatory care and so address health inequalities.^112^ Their success depends on clinicians identifying people for them.^113^
5	User preference	People with established epilepsy and those with other seizure presentations, such as non-epileptic attack disorder, usually want to avoid ED after an uncomplicated seizure,^114–117^ preferring to recover at home. Unnecessary conveyance to ED puts them at risk of iatrogenic harm and overinvestigation.^118–120^
6	Cost	Clinically unnecessary ED conveyance generates avoidable costs and contributes to ED overcrowding. In England, the annual cost to the NHS of unplanned hospital care for suspected seizures is ~£90 million.^121^

‘999’ is a telephone number for emergency calls in the UK.

AA, avoidable attendance; ED, emergency department; NHS, National Health Service.

RADOSS consists of four work packages (WP). WP1 is the main one. It involves a cohort study (WP1a) and a Knowledge Exchange (KE) study (WP1b). WP2 is smaller and focuses on validation via a second cohort study. WP3 focuses on ‘next steps’ on the journey to implementation of the tool in the NHS, and WP4 on dissemination (figure 1). According to Greene *et al*’s^64^ conceptual framework, the purpose of using a mixed-methods approach is both ‘development’ and ‘expansion’.

**Figure 1 F1:**
[figure not shown]
Summary of RADOSS project. Using four WPs, we will develop a risk prediction tool for people after a suspected seizure; we will validate the tool, plan its implementation and disseminate the findings. ED, emergency department; NHS, National Health Service; RADOSS, Risk of Adverse Outcomes after a Suspected Seizure; WP, work package.

### Routine data source: cured+

For WP1a and WP2, we will use a cutting-edge database called ‘CUREd+’. Currently being developed by the Centre for Urgent and Emergency Care Research,^64^ it will map UEC use by individuals served by the Yorkshire Ambulance Service (YAS) from 2011 to 2022. It contains records of all ambulance contacts and these are linkable to any subsequent ambulance, hospital (ED, inpatient) and death records (Office for National Statistics (ONS) mortality register). Further information is provided in table 3.

**Table 3 T3:** Key information about CUREd+ linked database

Issue	Detail
Linkage	CUREd+ is a prelinked data set. Events have been linked by NHS Digital using their algorithm based on NHS number, date of birth, postcode and sex.
Coverage of data	CUREd+ is new. Evidence from its predecessor CUREd (which mapped activity in the same area from 2011 to 2017 using a different approach^122^) indicates CUREd+ should have high data coverage. Evidence from CUREd and other work shows ~85% of individuals can have their ambulance and onward care records linked and so are suitable for inclusion.^104 123 124^ Wider work also shows those who can and cannot have their records linked do not markedly differ.^22^ CUREd+ could have even higher coverage due to more use of NHS numbers by ambulance services^125^ (which supports linkage).
Quality of data	The data contributing to CUREd were high in quality.^121 125 126^ Smyth^76^ examined ambulance patient care records (PCRs) for >22 000 patients. Most core clinical variables had <2% missing data and errors were rare. CUREd+ could have even higher quality due to the introduction of electronic PCRs (which support more consistent data capture).
Area covered by CUREd+ and suitability for RADOSS	England has 10 regional ambulance services. CUREd+ includes data from the Yorkshire Ambulance Service (YAS). The size of the population (~5.6 million) and geographical area (urban/rural mix, ~6000 square miles) served by YAS is similar to the average, as is its non-conveyance rate.^33^

NHS, National Health Service; RADOSS, Risk of Adverse Outcomes after a Suspected Seizure.

## Methods and analysis

### Work package 1

#### 
WP1a: retrospective cohort study 1

##### Purpose

Describe the pattern of calls for suspected seizure, the type of ambulance responses received and the characteristics of the patients accounting for them.Determine and compare the rate of death and recontact with the UEC system of those seen by the ambulance service for a suspected seizure who were and were not conveyed to ED.Determine the proportion of suspected seizure incidents conveyed to ED that resulted in an AA; develop predictive models for risk of death/recontact with the UEC system within 3 (and 30) days following conveyance and non-conveyance and risk of attendance at ED being classed an AA if conveyed.Combine the predictive models to form a draft tool that can potentially provide estimates of an individual’s risk of death/recontact with the UEC system if managed by non-conveyance; risk of death/recontact with the UEC system if managed by conveyance; and the risk of their attendance at ED being classed as an AA if conveyed.

To do this, a retrospective cohort of adults cared for a suspected seizure by YAS will be studied.

##### Identification

Index events will be identified by searching CUREd+ for persons managed by YAS for a suspected seizure between 1 February 2019 and 31 January 2020. Eligibility criteria are presented in table 4.

**Table 4 T4:** Participant inclusion and exclusion criteria for different WPs

WP	Inclusion criteria	Exclusion criteria

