**WP1a: retrospective cohort study 1**		
	Incident cared for by YAS. Person aged ≥16 years (no upper age limit). (Those ≥16 account for 90% of incidents.^62^ Incident occurred between 1 February 2019 and 31 January 2020.* ‘Chief complaint’ (or other complaint) selected by attending ambulance clinician on PCR was ‘convulsions/fitting/seizure’ OR, if empty, call handler coded it as AMPDS protocol 12 (‘Convulsions’). No restriction on type of ambulance response incident received (ie, could have been ‘Hear & Treat’, ‘See & Treat’, ‘See & Convey to ED’ or ‘See & Convey elsewhere’†).	The <1% of events coded as AMPDSC02. These relate to seizures in someone potentially pregnant. (Guidelines state these should be conveyed because of eclampsia risk.^47^

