###### Measure 2 (avoidable/unavoidable ED attendance)

Index events that resulted in conveyance to ED will be classified according to whether they resulted in an AA or not.

To determine this, the events will be assessed against O’Keeffe *et al*’s^9^ definition. Namely, a person has been involved in an AA if routine hospital coding for the attendance indicates it did not result in the person being investigated (except urinalysis, pregnancy test, dental investigation) or treated (except prescription, recording vital signs, dental treatment or guidance/advice), and they were discharged.

O’Keeffe’s system has advantages. It is generic, applicable to all ages,^9 70^ based on process of care rather than initial triage score and has been adopted by the NHS.^71^ It is also quick and routine data have been found to be sufficient to mean it can be applied to ~98% of attendances.^9^

A possible disadvantage is it assumes *all* investigations, treatments and admissions were clinically indicated. Some may have happened for other reasons (eg, routine or inappropriate administration of test). Thus, we shall describe the reasons why any WP1a cases satisfied the criteria for an unavoidable attendance. Moreover, via WP1b, we shall ask ED clinicians to what extent suspected seizure cases attending their EDs could satisfy the criteria of an unavoidable attendance based on routine practice. Should it prove warranted, a sensitivity analysis will be conducted with and without such cases.

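### Table 4 sets no call-source limit, so transfers and conveyances booked by another professional can enter the AA estimate and the models although the crew may have had no conveyance decision to make

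*Protocol article*

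**What the plan says.** The section on the routine data source says of CUREd+: "It contains records of all ambulance contacts". Under Identification, "Index events will be identified by searching CUREd+ for persons managed by YAS for a suspected seizure", with eligibility given in Table 4. For WP1a that table requires an incident handled by YAS, age 16 or over, a date in the study year, and a seizure complaint on the patient care record (chief or other) or, where that field is blank, AMPDS protocol 12. On response it says "No restriction on type of ambulance response incident received". The only exclusion is "The <1% of events coded as AMPDSC02" (possible pregnancy), for the stated reason that guidelines call for conveyance. The WP2 row repeats these criteria. Call source is not mentioned in either row.

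The intended use is narrower. The abstract describes a tool used on scene to "estimate the benefits an individual would receive if conveyed to ED and risks if not", and the section on whether such a tool could be developed says: "The information used by any risk prediction tool should reflect what is available to the clinician at the time conveyancing decisions are made".

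Three further rules decide where an incident goes. Measure 2 says: "Index events that resulted in conveyance to ED will be classified according to whether they resulted in an AA or not". The section on describing the sample counts See & Convey elsewhere as not conveyed to ED. The text after Table 4 makes the patient the unit of analysis, with the first recorded episode as the index event.

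**The concern.** A prediction model should be fitted on people who face the decision it is meant to inform. When another professional has already arranged the journey, or the patient is being moved between facilities, the crew may have nothing to decide. The plan already accepts this kind of argument: it removes C02 events, under 1% of the total, because guidelines say they should be conveyed. It says nothing about other journeys whose destination may have been settled in advance.

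Three results are exposed:

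- **The AA proportion.** An AA needs discharge with essentially no investigation or treatment. Patients already judged to need hospital may meet that less often.
- **The conveyed versus non-conveyed comparison.** Either group may contain people for whom the other course was never realistic.
- **The models.** Their coefficients and performance would partly describe people outside the target decision. Temporal validation could not show this, because WP2 uses the same eligibility.

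**Working it through.** **1. The plan's own figures.** The Sample size section gives 2567 index events with 103 target events (model 1), 2194 with 308 (model 2) and 2194 with 461 (model 3). These imply outcome proportions of 4%, 14% and 21% (461/2194 = 0.210). The Riley shrinkage criterion is n = P / ((S − 1) ln(1 − R²/S)). With P = 40, S = 0.9 and R² = 0.15 it gives 40 / (0.1 × 0.1823) = 2194, matching models 2 and 3. Model 1 comes from the second criterion, with S = R² / (R² + 0.05 × max R²) = 0.913 at a 4% outcome, giving 2567. R² = 0.15 is inferred, because supplementary file 3 is not shown. The figures reproduce, so this point does not rest on a sample-size error.

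**2. Where such an incident goes under the stated rules.**

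| Incident | Route |
|---|---|
| Transfer after an earlier qualifying episode for the same patient | Not the index event; counted as a recontact if inside the window |
| Transfer or booked journey, first episode, ending at an ED | Conveyed: models 1 and 3, AA denominator |
| Transfer or booked journey, first episode, ending elsewhere | Not conveyed to ED: can enter model 2 |

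In the last row, Measure 1 counts unscheduled inpatient care as recontact. Onward care that was the purpose of the journey could therefore be scored as an unsafe outcome of non-conveyance.

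**3. Effect on the AA proportion.** Assumptions: a share f of conveyed index events are such calls, with AA rate b; the documents give neither. If 21% holds among crew-decided conveyances, the observed proportion is (1 − f) × 0.21 + f × b.

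| f | b = 0% | b = 5% | b = 10% | b = 21% | b = 30% |
|---|---|---|---|---|---|
| 5% | 20.0% | 20.2% | 20.5% | 21.0% | 21.5% |
| 10% | 18.9% | 19.4% | 19.9% | 21.0% | 21.9% |
| 20% | 16.8% | 17.8% | 18.8% | 21.0% | 22.8% |

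For f of 5% to 10% and b of 0% to 5% the fall is 0.8 to 2.1 points. If 21% is instead taken as the mixed figure, the crew-decided proportion is (0.21 − f × b) / (1 − f): (0.21 − 0.0025) / 0.95 = 21.8% at f = b = 5%, and 0.21 / 0.90 = 23.3% at f = 10%, b = 0. That is 0.8 to 2.3 points. The size is similar either way. The effect vanishes when b = 21% and reverses above it.

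**4. Effect on the model 3 c-statistic.** Simulated mixture of 400,000 records, true c of about 0.70 among crew-decided conveyances, which have 21% AA:

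| f | b | c if predictors identify these calls | c if none does |
|---|---|---|---|
| 5% | 2% | 0.718 | 0.701 |
| 5% | 5% | 0.713 | 0.701 |
| 10% | 2% | 0.732 | 0.699 |
| 10% | 5% | 0.722 | 0.700 |
| 20% | 2% | 0.759 | 0.695 |

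A check by hand with c = 0.60 within each group, overall AA 21%, f = 10% and b = 2%: such calls make up 0.002/0.21 = 0.0095 of AA cases and 0.098/0.79 = 0.1241 of non-AA cases. If the model ranks all of them lowest, c = 0.9905 × 0.8759 × 0.60 + 0.9905 × 0.1241 + 0.0095 × 0.1241 × 0.60 = 0.644. With b = 5% it is 0.634. If no predictor identifies them, c is about 0.595 to 0.60. A rise therefore needs predictors that pick these calls out.

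**The case against.** The strongest reply is that nothing in the article shows such calls exist in the extract with a seizure complaint, let alone how many. Table 2 frames the problem as 999 calls, the complaint is chosen by the attending clinician, and the first-episode rule removes transfers that follow a qualifying episode. Broad eligibility also serves the aim of describing calls and responses. All of this stands. It limits the claim to what can enter, and it argues for a restriction at the analysis stage rather than a narrower cohort. It does not answer the gap, because the 999 framing is not carried into Table 4, which is where the article states eligibility.

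A reader might infer more: that these incidents sit only in the conveyed group, that they do lower the AA proportion, and that they inflate model 3. The documents do not support this. See & Convey elsewhere counts as not conveyed to ED, so some would fall on the other side. The AA shift depends on an assumed lower AA rate. A higher c-statistic needs call source, or a good proxy, among the predictors. Dispatch information is available, but the candidate list is to be informed by WP1b and is not shown. Nor is there a documentary basis for treating 21% as already diluted: it is the proportion implied by a sample-size calculation whose detail is in a supplement that is not shown.

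**Conclusion.** The point holds in a limited form. As written, Table 4 lets in incidents that may have involved no on-scene conveyance decision, in both the derivation and the validation cohort, and no flag or sensitivity analysis on call source is stated. The AA proportion, the comparison between groups and all three models could rest partly on people outside the target decision. The size is not known from the documents. An AA shift of 1 to 2 points rests on the assumed 5% to 10% share with 0% to 5% AA, and the direction of any c-statistic change depends on predictors not yet fixed. This is a cheap improvement worth making, not a demonstrated bias.

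**What to change.** Keep the full cohort for describing calls, responses and patients. For the AA proportion, the conveyed versus non-conveyed comparison and all three models, in WP1a and WP2 alike, restrict to incidents not recorded in the dispatch data as inter-facility transfers or health-professional bookings, and report how many are removed. If call source cannot be fully separated, report these results with and without the flagged incidents.

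The cost is one extra dispatch field and probably a small loss of index events. The counts left should be checked against 2567, 2194 and 2194. The model 3 requirement does not move with the AA proportion over the range examined (2194 at 17% to 21%), because the criterion that sets it does not involve prevalence.
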